## Abstract

**Background:**

The available care for people with psychosis in South Africa is inadequate to support personal recovery. Group peer support interventions are a promising approach to foster recovery, but little is known about the preferences of service users, or the practical application of this care model, in low- and middle-income countries (LMIC). This study aims to assess the acceptability and feasibility of integrating peer-led recovery groups for people with psychosis and their caregivers in South Africa into existing systems of care, and to determine key parameters in preparation for a definitive trial.

**Methods:**

The study is set in Nelson Mandela Bay Metropolitan district of the Eastern Cape Province, South Africa. The design is an individually randomised parallel group feasibility trial comparing recovery groups in addition to treatment as usual (TAU) with TAU alone in a 1:1 allocation ratio. We aim to recruit 100 isiXhosa-speaking people with psychosis and 100 linked caregivers. TAU comprises anti-psychotic medication-focused outpatient care. The intervention arm will comprise seven recovery groups, including service users and caregiver participants. Recovery groups will be delivered in two phases: a 2-month phase facilitated by an auxiliary social worker, then a 3-month peer-led phase. We will use mixed methods to evaluate the process and outcomes of the study. Intervention acceptability and feasibility (primary outcomes) will be assessed at 5 months post-intervention start using qualitative data collected from service users, caregivers, and auxiliary social workers, along with quantitative process indicators. Facilitator competence will be assessed with the GroupACT observational rating tool. Trial procedures will be assessed, including recruitment and retention rates, contamination, and validity of quantitative outcome measures. To explore potential effectiveness, quantitative outcome data (functioning, unmet needs, personal recovery, internalised stigma, health service use, medication adherence, and caregiver burden) will be collected at baseline, 2 months, and 5 months post-intervention start.

**Discussion:**

This study will contribute to the sparse evidence on the acceptability and feasibility of peer-led and recovery-oriented interventions for people with psychosis in LMIC when integrated into existing care systems. Results from this feasibility trial will inform preparations for a definitive trial and subsequent larger-scale implementation.

**Trial registration:**

Pan-African Clinical Trials Register PACTR202202482587686. Registered on 28 February 2022. https://pactr.samrc.ac.za/TrialDisplay.aspx?TrialID=21496.

**Supplementary Information:**

The online version contains supplementary material available at 10.1186/s40814-022-01232-8.

## Background

Globally, people with psychosis experience high levels of unmet needs, including social and economic hardships and human rights violations [1–3]. In South Africa, whilst most people with psychosis have access to primary care clinic-based outpatient services (primarily free provision of anti-psychotic medication) and inpatient care, there is limited community-based support for personal recovery. As a consequence, there are high readmission rates following discharge from hospital [4]. Recovery has been described as, “a deeply personal, unique process of changing ones’ attitude, values, feelings, goals, skills and/or roles” and “a way of living a satisfying, hopeful and contributing life even within the limitations caused by illness” [5]. The meaning of recovery, along with how we can best support and measure it, is shaped by cultural and social context. For example, it is proposed that family support has greater influence on recovery in low- and middle-income countries (LMICs) compared to high-income countries (HICs). Likewise, social connectedness and interdependence may be more pertinent indicators of recovery in LMICs [6].

Community-based psychosocial support offers benefits in terms of reducing symptom severity and improving functioning in people with psychosis [7–9]. Task-sharing, that is the delivery of circumscribed aspects of healthcare by less specialised workers with specialist support, is championed to increase coverage of community-based care. For real-world implementation to be successful, it is essential that task-shared approaches are integrated into existing health and social care systems. Furthermore, irrespective of the delivery agent, care should be person-centered [10], in order to be capable of fostering personal recovery. Highly structured psychosocial interventions may be favoured in LMIC settings to ensure non-specialist workers can become interventionists after only brief training within a task-sharing approach [11], but there are concerns that this approach could be to the detriment of truly person-centred care [10].

Peer support mental health interventions are provided by people with lived experience in one-to-one or group formats and can encompass emotional support, advocacy, and activities to promote social inclusion. There is a strong emphasis on personal recovery, by using a non-judgmental approach to address the issues of importance to service users. As experts by experience, peers are ideally placed to understand and support people with mental health conditions [12]. The World Health Organization (WHO) promotes peer support workers as a means of expanding coverage of community-based mental health care [13]. Peer support work is one modality of task-sharing, so it may be a useful strategy in settings with few specialist mental health professionals. Peer-led recovery groups have potential to achieve a person-centred approach, in which participants’ own needs and priorities are front and centre. The response to those needs is not preordained, but rather is a dynamic response arising from the diverse and real-life experiences of other group members. Such groups might also build peers’ self-confidence through meeting others, managing similar struggles, and reducing self-stigmatisation through positive role modelling. Peer support groups might also provide a good fit in LMIC settings where family and socially oriented mechanisms of recovery are prominent [6].

Whilst there is little evidence to date that peer support approaches provide greater benefits than usual care in reducing hospital readmission or relapse [14–17], there is some evidence that group peer support interventions are effective in supporting personal recovery in people with schizophrenia, depression, and bipolar disorder [17]. However, there is an absence of high-quality evidence for peer support approaches for people with psychosis in LMIC [18]. With the exception of one Chinese trial, all studies included in four recent systematic reviews were conducted in HIC [14, 16, 17, 19]. Peer-led mental health support groups are nevertheless used successfully in some LMIC. For example, the Users and Survivors of Psychiatry in Kenya supports a thriving network of service user-initiated and led peer support groups, with an emphasis on exercising respect for legal capacity (including treatment decisions) and advocacy activities [12]. The acceptability of the peer support model may be influenced by socio-cultural norms. For example, in Chile, where high importance is placed on professional and social hierarchies, service users seem less likely to accept support from an individual deemed not hierarchically superior [20]. Despite this emerging evidence, there has been little formal evaluation of the acceptability and feasibility of this model in LMIC [21–23]. In South Africa, recovery groups are not available as part of existing health and social care structures; evidence of the feasibility, acceptability, and potential benefits of these groups are needed to inform future investment in these kinds of services. To address this gap, we developed the peer-led recovery groups for people with psychosis in South Africa (PRIZE) intervention. This involved an 18-month formative phase that included scoping work; in-depth interviews with service users, caregivers, and service providers; and collaborator workshops (to be reported separately). Building on our model of group psychosocial rehabilitation previously piloted in South Africa’s North West Province [24, 25], we designed a task-shared model delivered in two phases: an auxiliary social worker (ASW)-facilitated phase followed by a peer-facilitated phase. Both emphasise peer involvement in group delivery, underpinned by a strong recovery orientation.

The overall aim of this randomised feasibility trial is to assess the acceptability and feasibility of the PRIZE intervention for people with psychosis in South Africa, and to determine key parameters in preparation for a definitive trial. The objectives, which span a process evaluation, the assessment of trial procedures, and a preliminary outcome evaluation are:

### Process evaluation

1.a. To assess the acceptability and feasibility of the intervention from the perspective of service users, caregivers and service providers (primary outcomes)1.b. To assess the skills and competence of ASW and peer facilitators

### Assessment of trial procedures

2.a. To establish the validity of quantitative outcome measures of recovery, unmet needs, and functioning2.b. To assess trial procedures including the acceptability and feasibility of fidelity measures, recruitment and retention rates, and the suitability of an individually randomised design2.c. To synthesise outcome data to inform the sample size of a definitive trial

### Preliminary outcome evaluation

3.a. To explore the potential effectiveness of recovery groups plus treatment as usual (TAU) compared to TAU alone in terms of service user functioning, personal recovery, unmet needs, internalised stigma, health service use, relapse, medication adherence, and alcohol consumption; and caregiver burden

## Methods

### Setting

The study site is in the Eastern Cape province, which has the lowest Gross Domestic Product per capita of all nine provinces in South Africa. We will work in the Nelson Mandela Bay Metropolitan district (population 1,152,115) that includes the city of Gqeberha, two small towns and agricultural areas. There are 41 primary health care facilities (“clinics”) and eight hospitals (including a psychiatric hospital). Eight of the clinics provide mental health care delivered by psychiatric nurses. Available care includes free medication for people with psychosis living in the community. The clinics do not provide psychosocial support for people with psychosis. Seven of these eight clinics serve a predominantly isiXhosa-speaking population (the target population for the study). These seven study sites are in low-income areas with a concentration of low education levels, unemployment, and poor health outcomes.

### Study design

The design is an individually randomised parallel group feasibility trial comparing recovery groups in addition to TAU compared to TAU alone in a 1:1 allocation ratio (see Fig. 1). We will use mixed methods to address our study objectives. Data will be collected at baseline, 2 months, and 5 months post-intervention start.

**Fig. 1 Fig1:**
[figure not shown]
PRIZE study flow chart

### Participants

Trial participants are service users and caregivers. Service user eligibility criteria are as follows: (i) clinical diagnosis of psychosis associated with enduring disability, including schizophrenia, schizoaffective disorder or dual diagnosis of schizophrenia, and alcohol use or other substance use disorder; (ii) ≥18 years old; (iii) speak isiXhosa; (iv) have capacity to give informed consent to study participation; and (v) plan to stay in the area for the next 6 months. Caregiver eligibility criteria are as follows: (i) primary caregiver for a participating service user; (ii) ≥18 years old; (iii) speak isiXhosa; and (iv) plan to stay in the area for the next 6 months. Additional participants for the process evaluation are recovery group facilitators and supervisors (ASWs and a social worker), and TAU service providers (psychiatric nurses and clinic managers). A subset of potential participants who meet the eligibility criteria but who decline to participate in the trial will be invited to participate in a brief qualitative interview. The participant timeline is presented in Fig. 2.

**Fig. 2 Fig2:**
[figure not shown]
PRIZE participant timeline

#### Recruitment

We estimate that a minimum of 15 people with psychosis access care at each participating clinic. Information leaflets and posters will be used to provide initial sensitization to the study in the clinic waiting areas. At these clinics, during all regular scheduled appointments for people with psychosis taking place during the recruitment period, psychiatric nurses will provide initial brief information about the study and ask for verbal consent for a PRIZE staff member to speak with them or contact them. The nurse will use a script to clarify that the person has no obligation to participate and that non-participation will not affect their care. Service users who agree will be directed to speak with an assessor immediately following their clinic appointment. The assessor will give initial verbal information on the study to the service user in isiXhosa and complete a screening checklist for eligibility criteria (except capacity to consent). A home visit will then be arranged for eligible service users who are interested in participating. Service users will be invited to identify a primary caregiver or a person of their choice to participate in the study and to be present at the home visit. To recruit a pragmatic and inclusive sample, service users who do not have an available caregiver will still have an opportunity to participate in the study.

At the home visit, the trial social worker will give verbal and written information on the study in isiXhosa. If the participant is interested in participating, the social worker will conduct the full capacity assessment, consent procedures, and baseline assessment. All procedures will be conducted privately. If the potential participant needs time to consider the information, a separate meeting will be scheduled within the following week. The subset of eligible but declining participants will be contacted by telephone by the study coordinator to invite them to participate in the qualitative interview.

#### Consent

Service user capacity to consent will be assessed by the trial social worker, who will be trained by an isiXhosa-speaking psychiatrist. We will use a modified capacity assessment form shown to be feasible in other LMIC settings [26, 27]. Participants assessed not to have decision-making capacity will be excluded, as well as their caregiver. The trial social worker will obtain informed consent for service users with capacity and their caregivers. For participants who are unable to write, a thumb impression will be recorded, along with a witness’ signature. To compensate for their time, participants will be provided with a R150 grocery voucher at each assessment time point. Written informed consent for ASWs, nurses, clinic managers, and declining individuals participating in qualitative interviews will be obtained by the study coordinator.

#### Sample size

We will aim to recruit a total of 100 service users and 100 linked caregivers. Assuming 20% attrition, ~40 service users and ~40 caregivers will receive the intervention and each recovery group will have a mean size of 11.4 participants (5–6 service users and 5–6 caregivers). We envisage these are sufficient numbers to adequately assess the acceptability and feasibility of the intervention (Objective 1.a), whilst accounting for potential differences in experience due to variations between clinic catchment areas, e.g. in socio-economic status, accessibility of venue, and community resources.

For the validation of outcome measures (Objective 2.a), we estimate that our final sample size of *n*=80 service users will give >90% power to detect correlations of ≥0.4 and 70% power to detect a standardised effect size of 0.28 for internal sensitivity to change at 2 months compared to baseline. The effect size of 0.28 is based on a mean change of 5 from baseline to follow-up, with a standard deviation of 15 and an intraclass correlation of 0.05. As this is a feasibility study, it is not powered to detect differences in outcome measures between treatment arms (Objective 3.a). We anticipate a total of approximately *n*=4 ASWs, *n*=7 service user facilitators, and *n*=7 caregiver facilitators will be sufficient to make an exploratory assessment of facilitator competence (Objective 1.b).

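### The effect size of 0.28 and 70% power for sensitivity to change fit about eight clinics, not the trial's seven (0.27, about 67%), and the plan does not say whose change of 5 is meant

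*Protocol article*

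**What the plan says.** The Sample size section of the protocol article sets the recruitment target ("We will aim to recruit a total of 100 service users and 100 linked caregivers") and allows for 20% attrition. For the validation objective it works with "our final sample size of *n*=80 service users" and states "70% power to detect a standardised effect size of 0.28 for internal sensitivity to change at 2 months compared to baseline". The effect size is said to rest on "a mean change of 5 from baseline to follow-up, with a standard deviation of 15 and an intraclass correlation of 0.05". The section gives no number or size of clusters and no significance level.

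The cluster count comes from elsewhere. Under Setting, eight clinics in the district provide mental health care, but "Seven of these eight clinics serve a predominantly isiXhosa-speaking population", and those seven are the study sites. The overview of the recovery groups likewise describes seven groups, one per clinic catchment area.

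The 80 are both arms together: allocation is 1:1, and the Sample size section says that "Assuming 20% attrition, ~40 service users and ~40 caregivers will receive the intervention". Under Assessment of trial procedures, internal and external responsiveness are to be calculated from baseline to 2 and 5 months, with no mention of arm.

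**The concern.** There are two separate points.

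The first is arithmetic. The unadjusted effect is 5/15 = 0.333, so the step down to 0.28 must be the allowance for clustering by clinic. That allowance depends on the number of service users per clinic, and the value that yields 0.28 is not the one that seven clinics give.

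The second is what the change of 5 describes. The calculation applies it to all 80 service users, yet about half receive no recovery groups. If 5 is the change hoped for in people who attend the groups, the pooled mean is smaller unless those on TAU improve as well, and power falls quickly as the pooled mean shrinks. A small pooled change could then reflect the mix of arms rather than a measure that fails to respond.

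This is the only power figure given for sensitivity to change. The section's caveat about not being powered concerns differences between arms (Objective 3.a), so it does not cover this claim.

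**Working it through.** **Inputs.** Mean change 5, SD 15, ICC 0.05, n = 80, stated effect 0.28 and power 70% (Sample size); 7 clinics (Setting); 1:1 allocation (Study design). Assumed: two-sided 5% level. A one-sided 5% test at 0.28 would give 80.5%, so the two-sided reading is the one that fits the stated 70%.

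**Formulas.** Power (normal) = Φ(d√n − 1.96), checked with the noncentral t on n − 1 degrees of freedom. Clustering: d = (5/15)/√DE, with DE = 1 + (m − 1) × 0.05 and m = n / number of clinics.

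**Step 1: the plan's own figure.** With d = 0.28 and n = 80, d√n = 2.504 and power is 70.7% (normal) or 69.6% (t). The 70% therefore follows from 0.28.

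**Step 2: which cluster size gives 0.28.** Solving (0.333/0.28)² = 1 + (m − 1) × 0.05 gives m = 9.3. Any value that rounds to 0.28 (0.275 to 0.285) needs m between about 8.4 and 10.4, which is 7.7 to 9.6 clinics for 80 people. The only whole numbers in that range are 8 and 9. With 8 clinics, m = 10, DE = 1.45, d = 0.277, and power is 69.7% (normal) or 68.6% (t).

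**Step 3: the seven study clinics.** m = 80/7 = 11.43. DE = 1 + 10.43 × 0.05 = 1.521. d = 0.333/1.233 = 0.270. d√80 = 2.417. Power is 67.6% (normal) or 66.6% (t). By the normal formula, about 88 analysed service users in seven clinics would be needed for 70%.

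**Step 4: how power depends on the two arms' changes.** Seven clinics, n = 80, SD 15 within each arm. The pooled mean is (I + T)/2 and the pooled SD is √(225 + ((I − T)/2)²), where I and T are the intervention and TAU changes. All I and T values are assumptions, since the protocol gives no arm-specific change.

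| I | T | Pooled mean | Pooled SD | d after clustering | Power (t) |
|---|---|---|---|---|---|
| 5 | 5 | 5 | 15.0 | 0.270 | 67% |
| 5 | 2.5 | 3.75 | 15.05 | 0.202 | 43% |
| 5 | 0 | 2.5 | 15.2 | 0.133 | 22% |
| 7.5 | 2.5 | 5 | 15.2 | 0.267 | 65% |
| 10 | 0 | 5 | 15.8 | 0.256 | 62% |

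The normal formula gives 67.6%, 43.9%, 22.1%, 66.4% and 63.1% for the same rows. The first three rows take 5 as the intervention-arm change. The first and the last two average 5 over both arms. If the SD of 15 is instead the pooled SD, every row that averages 5 gives 67% (t).

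**The case against.** The arithmetic gap is small: power moves from 70% to about 67%, and no sample size, analysis or decision depends on those three points. The cluster size of 11.4 is inferred from other sections, because the Sample size section states none. All of that stands, and it is why the point is minor. It does not remove the mismatch: the documents fix seven clinics, and seven clinics do not give 0.28.

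A reader might infer that 70% holds only if the TAU arm improves as much as the intervention arm. The documents do not support that. The calculation needs an average change of 5 over the 80, and any split with that average gives about 62–67%. Nor does the protocol say that 5 is the intervention-arm change or that TAU participants will stay unchanged. TAU is active care, with medication, symptom checking and basic psychoeducation. The 22% and 43% are therefore conditional illustrations and not the trial's power.

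A reader might also infer that a responsive measure would be dropped from the definitive trial. No rule of that kind is stated. Responsiveness is simply to be calculated, alongside convergent correlations, external responsiveness, Cronbach's alpha and factor analysis.

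Finally, pooling is defensible for validation, since relating change in a measure to change in a reference measure benefits from a spread of change. Making the intervention arm the main estimate would halve the sample and is a trade-off, not a correction. By-arm results also have to respect the masking of data analysts that the protocol promises.

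**Conclusion.** The point holds and is minor. The stated effect size and power match about eight clinics. For 80 service users in the seven study clinics, the same inputs give 0.27 and about 67% (66.6% by t, 67.6% by the normal formula), assuming a two-sided 5% test, equal clinic sizes and the usual design effect.

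That 67% is itself conditional on a mean change of 5 averaged over both arms, which the text neither states nor excludes. If 5 is the intervention-arm change, pooled power runs from about 22% to 67% as the TAU change goes from 0 to 5. The practical weight is limited: this is a secondary validation objective of a feasibility trial whose primary outcomes are acceptability and feasibility.

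**What to change.** In the Sample size section, restate the figure as an effect size of 0.27 and about 67% power, for 80 service users in seven clinics with a two-sided 5% level (if that is what was used), conditional on an average change of 5 over both arms.

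Under Assessment of trial procedures, add the standardised response mean with its 95% confidence interval for each arm, next to the pooled estimate, so that a small pooled change is not read as an unresponsive measure. Labelling the arms by code keeps the analysts masked.

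The cost is a slightly less favourable stated power and one extra table. No further participants or data are needed.
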